## SPECIFIC AIMS

### *Primary Aim*

We will accomplish a 20% reduction in hospitalization cost for selected hospitalized adults who would normally have been admitted to the hospital.

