## Subject Enrollment

### Methods of enrollment, Procedures for obtaining consent

- Decision to admit or observe made by emergency room team or by an ambulatory clinician who would otherwise admit her/his patient.
- Participant is pre-screened by a research assistant for primary diagnosis, age, and residence within 7.5 miles via the electronic medical record.
- If participant meets those criteria, the emergency room team or ambulatory clinician will ask the patient/caregiver if the research assistant can approach the patient regarding the home hospital study.
- If participant agrees, the research assistant will describe the program, answer initial questions, and further assess whether the participant meets inclusion/exclusion non-clinical (e.g., social) criteria. The RA will then contact the on-call MD to assess clinical criteria by EHR review.
- If the participant has interest in the program and meets inclusion/exclusion criteria, the on-call MD (either in-person or via a live video visit facilitated by the research assistant) will obtain written informed consent of the participant to enroll in the home hospital program.
- For a subject known to be without capacity, any of the following individuals (listed in general order of preference) may give consent provided they are on-site and able to sign the informed consent (the patient will assent):
  - court appointed guardian with specific authority to consent to participation in research or authority to make health care decisions for a class of diagnostic and therapeutic decisions inclusive of the proposed research;
  - health care proxy/person with durable power of attorney with specific authority for making health care decisions inclusive of the proposed research; or
  - spouse, adult child, or other close family member who knows the subject well and has been involved in their care.
  - When surrogate consent is relied upon, the Investigator must ensure that the surrogate understands that his or her decisions should be based on "substituted judgment." This means that the decision reflects a potential subject's own views when s/he had the capacity to express them. If a potential subject did not previously express a view on the matter, the surrogate should make the decision based on the potential subject's best interests.

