## Statistical methods

### *Home hospital vs traditional hospital*

#### *Quantitative*

We plan to form 3 different control groups (with groups listed in order of preference):

1. Patients who were deemed eligible for home hospital, but the service was full (and they were not enrolled subsequently if the service was no longer full);
2. Patients who were deemed eligible for home hospital, but lived outside of the 7.5-mile catchment area; and
3. Patients who were admitted to the hospital.

For each control group, we will use propensity score weighting, adjusting for covariates of interest (see table above), baseline functional status, and DRG. We will be cognizant of over-adjustment depending on our final sample size for each group above. If possible, we will use only group 1 above, as it is the strongest. If we have insufficient control group sample size, we may choose to combine groups 1 and 2 above.

The primary outcome (hospitalization cost) will be assessed using a generalized linear model assuming a gamma distribution with a log link. We will use a multivariable regression approach for secondary

outcomes, using logistic regression for binary outcomes and non-transformed linear regression for normally distributed continuous outcomes as appropriate.

We *a priori* plan to perform a subgroup analysis that does not involve any outlier participants, should this occur. We also *a priori* plan subgroup analyses by diagnosis, by age group, by disposition, by location of admission (e.g., ED, floor, clinic, and home), and by daily activity level. We also *a priori* plan to analyze our outcomes with means, but also with median and interquartile ranges, which are less subject to outlier effects. We may choose to employ non-parametric tests of significance should our data be nonparametric.

We *a priori* plan to adjust our secondary analyses using the Benjamini-Hochberg method. We *a priori* choose a false-discovery rate of 0.20.

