## Power analysis

### *Standard Home Hospitalization*

Our recent RCT data suggest that at 90% power, we will require 38 patients in each arm. However, we also have prespecified a smallest important difference of \$1000, for which we will need 144 patients in each arm at 90% power.

For 30-day readmission, we will require 110 patients in each arm at 90% power (23% vs 7%). If the effect size is indeed smaller, for example 23% vs 15%, we will need 528 patients in each arm. However, we will not be able to power around a smallest important difference of 3%, for which we would need 4006 patients in each arm.

For percentage with a safety event, we will require 641 patients in each arm at 90% power and 493 patients in each arm at 80% power (15% vs 9%).

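### Control group 3 has no eligibility condition and no rule limiting its use; if it is used, residual confounding could bias the cost and safety comparisons, probably toward home hospital

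*Protocol*

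**What the plan says.** The Primary Aim is a 20% cost reduction in "selected hospitalized adults who would normally have been admitted to the hospital".

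Under Statistical methods (Home hospital vs traditional hospital, Quantitative), three control groups are planned, "with groups listed in order of preference":

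1. "Patients who were deemed eligible for home hospital, but the service was full";
2. "Patients who were deemed eligible for home hospital, but lived outside of the 7.5-mile catchment area";
3. "Patients who were admitted to the hospital".

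Each group is to be propensity weighted on the Covariates of Interest, baseline functional status and DRG, and the authors reserve judgement on over-adjustment. On choosing among the groups the section says "If possible, we will use only group 1 above, as it is the strongest", and it allows groups 1 and 2 to be combined if controls are too few. Group 3 appears nowhere in that choice.

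The section on early transfer to home hospital adopts the same analysis, with one added variable for patients first turned away because the census was full.

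For the $1,000 smallest important difference in cost, the Power analysis says "for which we will need 144 patients in each arm at 90% power".

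**The concern.** Home patients pass a long clinical screen under Inclusion/exclusion criteria. It removes, among others, patients with acute delirium, patients above cut-offs on CURB65, SMARTCO, qSOFA or the heart-failure scores, and patients thought likely to need CT, MRI, endoscopy, transfusion or surgery. Controls in groups 1 and 2 have been found eligible. Controls in group 3 need only have been admitted.

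If a group 3 result were reported for the primary cost endpoint, patients screened as low-risk would be set against inpatients who were not screened. Ineligible inpatients are likely to cost more and to have more adverse events, so home hospital could look better without any true effect. Length of stay, readmission and adverse events are exposed in the same way.

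Early transfer may be more exposed. Under Subject Enrollment, floor patients must be improving and unlikely to deteriorate or to need an invasive procedure before they go home; group 3 requires neither. Adverse events are a non-inferiority outcome in that comparison, so a bias of this kind would make non-inferiority easier to claim.

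**Working it through.** **1. What the weighting can reach.** Set the exclusions beside the Covariates of Interest table.

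- Partly reached: hemodialysis (comorbidity type), infarction and surgery (DRG), general acuity (InterQual leveling) and frailty (PRISMA-7, baseline function).
- Not listed: delirium at admission, the pneumonia, urinary, other-infection and heart-failure score cut-offs, and the on-call physician's view that imaging, endoscopy or transfusion is likely.

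A patient who fails an absolute exclusion has no counterpart among home patients. If the excluding feature is not in the propensity model, that patient still receives weight as though eligible. Several weighting variables also come from patient interview. The protocol provides for collecting them from people who decline, but does not mention inpatients who were never approached.

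**2. Cost scale implied by the sizing.** No mean, SD or alpha is given, so 144 per arm cannot be reproduced independently; it can only be inverted. Two-sided alpha 0.05 is an assumption. It is supported by the neighbouring readmission figures: with a continuity correction, 23% vs 15% gives 528 and 23% vs 20% gives 4006, both as stated.

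- SD = 1000 × √(144/2) / (1.960 + 1.2816) = $2,618
- SE of a difference at 144 per arm = 2618 × √(2/144) = $308

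**3. Illustrative bias in dollars.** Let q be the ineligible share of the weighted controls and k their excess cost in SDs. Both are assumed. Bias = q × k × 2618. The chance of a falsely significant saving when there is no true effect is Φ(bias/308 − 1.96).

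| q | k = 0.5: bias, chance | k = 1: bias, chance |
|---|---|---|
| 10% | $131, 6% | $262, 13% |
| 20% | $262, 13% | $524, 40% |
| 30% | $393, 25% | $785, 72% |

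If ineligible patients cost less, the sign reverses.

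**4. The same question on the relative scale.** Let s be the true saving, r the cost of ineligible relative to eligible inpatients, q the ineligible share before weighting, and u the share of the imbalance left after weighting. Apparent saving = 1 − (1 − s) / (1 + u·q·(r − 1)).

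| s, q, r | u = 1 | u = 0.5 | u = 0.25 |
|---|---|---|---|
| 20%, 0.5, 1.5 | 36% | 29% | 25% |
| 20%, 0.2, 1.2 | 23% | 22% | 21% |
| 20%, 0.5, 0.8 | 11% | 16% | 18% |
| 0%, 0.5, 1.5 | 20% | 11% | 6% |

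For example, in the first cell 1 − 0.8/1.25 = 36%. A true 20% saving could be overstated or understated, and weighting shrinks the error without a guarantee of removing it.

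**The case against.** The strongest reply is that the protocol already treats group 3 as its weakest comparator. It is ranked last, group 1 alone is intended, and the written fallback stops at groups 1 and 2. Each group is analysed separately, so a group 3 result would not contaminate a group 1 result. This stands. A reader might infer that the primary comparison will be made against unscreened inpatients; the text does not support that.

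A reader might also infer that the cost saving is inflated as a matter of fact. The documents do not support that either, since no figure fixes the size or direction. Group 3 would also hold eligible patients, people who declined, and people excluded only on social grounds. Some clinical exclusions are conditional or advisory. DRG, comorbidity type and InterQual leveling remove part of the imbalance.

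The illustration has limits. Its shares and excess costs are assumed. It uses an unweighted normal comparison with 144 per arm and a constant SD, whereas the plan specifies a weighted gamma model with a log link and gives no size for group 3. That the controls of the earlier RCT met the present criteria is itself an inference, because the Background says the criteria changed.

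Cohort extraction for a third-choice comparator might be left to a statistical analysis plan, which is not at hand. The protocol, however, defines group 3 itself and plans to form and weight it. Its preference is worded softly, and nothing bars group 3 from primary use.

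**Conclusion.** The point holds in conditional form. Group 3 lacks the eligibility condition that groups 1 and 2 carry, and the protocol neither says when it may be used nor confines it to sensitivity analysis. If it is used, the listed weighting variables cannot be relied on to make it comparable. Residual confounding could then bias the cost and safety comparisons, including those for early transfer.

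Bias toward home hospital is the more plausible direction, because the clinical exclusions remove sicker and more resource-intensive patients. The size is unknown. Under an assumed 10% to 30% ineligible share and 0.5 to 1 SD excess cost, it is roughly $130 to $790, or 13% to 79% of the $1,000 smallest important difference. The 6% to 72% chances of a false finding belong to those assumptions and are not properties of the plan. If group 1, or groups 1 and 2, supply enough controls and group 3 is not used, the problem does not arise.

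**What to change.** Redefine group 3 along these lines: *patients admitted to the hospital who, on data available at the time of the admission decision, meet the protocol's diagnosis, age and clinical inclusion and exclusion criteria that can be ascertained from the electronic record, including the disease-specific score cut-offs; these criteria are applied before propensity weighting.* Add that any group 3 comparison, in the main or the early-transfer analysis, is reported as a sensitivity analysis only.

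The screening route already exists for enrolment: "The RA will then contact the on-call MD to assess clinical criteria by EHR review". The stated sample sizes do not change, because they come from RCT data.

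The cost is some chart filtering and a smaller group 3. Criteria that rest on the on-call physician's judgement, such as likely procedures, carry a risk of hindsight when applied retrospectively. Social criteria are often not in the record. Neither can be fully applied, which is a further reason to keep group 3 for sensitivity only.

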### The home hospital model and prior clinical studies

The home hospital model of care provides in-home acute care to acutely ill patients who would normally be admitted to a traditional hospital. This sort of substitutive care has been provided around the world for decades. Earlier studies of home hospital care in Australia, Italy, Spain, and elsewhere demonstrated lower costs, while either maintaining or improving on quality, safety, and patient experience. In the United States, 2 principle studies of the home hospital model have demonstrated that a sizeable proportion of acute care can be delivered in the home with equal quality and safety, 20% reduced cost, and 20% improved patient experience.

In late 2016, we launched a randomized controlled trial (RCT) of home hospital care, the first RCT to be performed in the US context. We first performed a small pilot with 21 patients. In short, we found the same as our international colleagues: cost savings while maintaining safety, quality, and patient experience.

In July, 2017, we amended our protocol and relaunched the RCT at Brigham and Women's Hospital (BWH) and Brigham and Women's Faulkner Hospital (BWFH) with several key improvements. We added to our catchment zone (5-miles around both BWH and BWFH, not just BWH), removed certain exclusions (eg dementia), and added certain conditions (eg gout exacerbation). We subsequently enrolled 91 patients and published our findings, which corroborated prior work: lower cost, lower utilization, and improved physical activity. No large changes in quality or safety were observed, although the study was not powered to closely scrutinize these data.

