### *Secondary Aims*

We will accomplish the following for the above-mentioned selected hospitalized adults:

- reduce health care utilization;
  - For example: decreased length of stay, number of labs/imaging, readmissions, ED visits
- maintain or improve on patient safety;
  - For example: reduced risk of delirium, falls
- maintain or improve on quality of care;
  - For example, high-value: increase in appropriate antibiotic selection, hours of sleep

- For example, low-value: decrease in use of urinary catheter, inappropriate medications in the elderly
- maintain or improve on functional status and quality of life; and
  - For example: increase in EuroQol-5D-5L, activities of daily living scale
- improve absolute patient experience by 20%.
  - For example: increase in 3-item care transition measure, PROMIS experience measures

***Please refer to our performance measures below for more details regarding the definitions and sources for each of these measures.***

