### Health Care Utilization

| Measure                                                | Source                                                       | Day(s) Obtained |
|--------------------------------------------------------|--------------------------------------------------------------|-----------------|
| Length of stay, days                                   | RA via MD/RN for home patients; RA EHR review for inpatients | Discharge       |
| IV medication, days                                    | As above.                                                    | Daily           |
| Intravenous fluids, days                               | RA via EHR                                                   | Daily           |
| Intravenous diuretics, days                            | RA via EHR                                                   | Daily           |
| Intravenous antibiotics, days                          | RA via EHR                                                   | Daily           |
| Oxygen requirement, days                               | RA via RN                                                    | Daily           |
| Nebulizer treatment, days                              | RA via EHR                                                   | Daily           |
| Imaging, #                                             | As above. +30 will be cross-checked with Partners data.      | Daily, +30      |
| Lab Orders, #                                          | As above.                                                    | Daily, +30      |
| MD sessions, # of notes                                | As above.                                                    | Daily, +30      |
| Consultant sessions, # of notes                        | As above.                                                    | Daily, +30      |
| PT/OT sessions, # of notes                             | As above.                                                    | Daily, +30      |
| Disposition (routine, SNF, home health, other)         | RA via MD/RN for home patients; RA EHR review for inpatients | Discharge       |
| PCP follow-up within 14 days, y/n                      | RA via pt phone call, cross-checked with Partners data.      | +30             |
| SNF utilization, days                                  | As above.                                                    | +30             |

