#### Quality: High-Value Care

| Measure                                 | Source                                                       | Day(s) Obtained |
|-----------------------------------------|--------------------------------------------------------------|-----------------|
| Pain management                         | RA via MD/RN for home patients; RA EHR review for inpatients | Daily           |
| Hours of sleep per day                  | RA via activity tracker                                      | Daily           |
| Hours of sleep per night                | RA via activity tracker                                      | Daily           |
| Hours of activity per day               | RA via activity tracker                                      | Daily           |
| Hours of activity per night             | RA via activity tracker                                      | Daily           |
| Hours of sitting upright per day        | RA via activity tracker                                      | Daily           |
| Hours of sitting upright per night      | RA via activity tracker                                      | Daily           |
| Daily steps                             | RA via activity tracker                                      | Daily           |
| Pneumonia                        |                                                              |                 |
| Pneumococcal vaccination if appropriate | RA via EHR                                                   | Discharge       |
| Influenza vaccination if appropriate    | RA via EHR                                                   | Discharge       |

|                                                                                  |                                                                             |                |
|----------------------------------------------------------------------------------|-----------------------------------------------------------------------------|----------------|
| Smoking cessation counseling if appropriate                                      | RA via EHR                                                                  | Discharge      |
| Heart Failure                                                             |                                                                             |                |

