**Patient Functional Status and Quality of Life**

| Measure        | Source         | Day(s) Obtained                |
|----------------|----------------|--------------------------------|
| EuroQol -5D-5L | RA via patient | Admission, discharge, +30      |
| SF-1           | RA via patient | -30, admission, discharge, +30 |

|                                                                                                     |                |                                |
|-----------------------------------------------------------------------------------------------------|----------------|--------------------------------|
| Activities of daily living: admission to discharge; admission to 30-day post-discharge              | RA via patient | -30, admission, discharge, +30 |
| Instrumental activities of daily living: admission to discharge; admission to 30-day post-discharge | RA via patient | -30, admission, discharge, +30 |
| Patient Health Questionnaire-2                                                                      | RA via patient | Admission, discharge, +30      |
| PROMIS Emotional Support Short Form 4a                                                              | RA via patient | Admission, discharge, +30      |
| Days at home since discharge                                                                        | RA via patient | +30                            |
| Milestones                                                                                   |                |                                |
| Walk around ward/home                                                                               | RA via RN      | Discharge                      |
| Get to (non-commode) bathroom                                                                       | RA via RN      | Discharge                      |
| Walk 1 flight of stairs                                                                             | RA via RN      | Discharge                      |
| Visit with friends/family                                                                           | RA via patient | Discharge                      |
| Walk outside around my home                                                                         | RA via patient | +30                            |
| Go shopping                                                                                         | RA via patient | +30                            |

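### Two planned home-versus-hospital subgroups, disposition and daily activity level, appear to be formed after treatment starts, so effects within them are prone to bias

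*Protocol*

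**What the plan says.** The Quantitative part of the Protocol's statistical methods for home hospital versus traditional hospital says the investigators "plan subgroup analyses by diagnosis, by age group, by disposition"; from disposition onward the list reads "by disposition, by location of admission (e.g., ED, floor, clinic, and home), and by daily activity level". Nothing there restricts these variables to values known at entry or calls any of the breakdowns descriptive.

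The data-collection tables show when each variable arises:

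- The Health Care Utilization table lists "Disposition (routine, SNF, home health, other" (the list closes there), obtained at discharge. A secondary aim is to "reduce health care utilization".
- The Quality: High-Value Care table lists "Hours of activity per day" and daily steps, taken from an activity tracker every day of the episode.
- Neither disposition nor activity is in the Covariates of Interest table.

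The background section on prior clinical studies summarises the investigators' earlier randomized trial as showing "lower cost, lower utilization, and improved physical activity".

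Confounding is to be handled by propensity score weighting on the covariates of interest, baseline functional status and DRG.

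**The concern.** A subgroup analysis compares the arms among patients who share a characteristic. If that characteristic is fixed before treatment, the comparison keeps whatever balance the weighting achieved. If treatment can change it, the same label picks out different kinds of patient in the two arms. Suppose home care makes patients more active and sicker patients are less active. A home patient who reaches a given activity level is then, on average, sicker than a hospital patient at that level. Severity also raises cost, so the arms differ within the stratum for a reason other than the effect of home hospital.

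Weights built from baseline covariates balance the arms as whole groups. They are not designed to balance arms within strata defined by something that happens later. The Protocol would therefore report, as pre-specified, subgroup effects that can differ from the true effect even when that effect is the same in everyone. The early-transfer and paramedic analyses refer back to the same methods, so the wording may carry over to them.

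**Working it through.** **1. Timing and role of each subgroup variable**

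| Variable | When fixed | Listed as | Evidence in the Protocol that treatment moves it |
|---|---|---|---|
| Diagnosis, age group, location of admission | At entry | Entry criteria or covariates | Not applicable |
| Disposition | Discharge | Utilization outcome | No result given; reducing utilization is an aim |
| Daily activity level, read as tracker activity | Daily during the stay | Quality outcome | Earlier trial reported improved physical activity |

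**2. No stated figure to reproduce.** The Protocol gives no sample size, power or effect for these subgroups. Whether bias arises can be reasoned from the table; its size needs assumptions.

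**3. Mechanism under a simple model.** All slopes are assumed. Let U be severity, standard normal and balanced between arms, with A = 1 for home and 0 for hospital.

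- Activity = g·A − U + e, with e standard normal.
- Mean cost is proportional to R^A · exp(b·U), where R is the true cost ratio in every patient.

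At a fixed activity level x, E[U | x, A] = −(x − g·A)/2, and the residual variance of U is 1/2 in both arms. Home patients are thus sicker by g/2, and the apparent cost ratio is R·exp(b·g/2). With R = 0.80, the Protocol's target 20% reduction:

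- g = 0.5, b = 0.3: 0.80 × exp(0.075) = 0.80 × 1.078 = 0.86
- g = 1.0, b = 0.5: 0.80 × exp(0.25) = 0.80 × 1.284 = 1.03
- g = 0: 0.80, no bias

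Broader strata dilute this, because patients within them vary in activity.

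**4. Simulation with broader strata.** This used 2,000,000 patients per scenario, gamma costs (shape 2), arms exchangeable at baseline, and activity split at its median. The log-odds of routine discharge were 1.0 + g·A − U. Estimated cost ratios when the true ratio is 0.80 in everyone:

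| g | b | All | Activity high / low | Routine / non-routine | Baseline severity high / low |
|---|---|---|---|---|---|
| 0 | 0.3 | 0.801 | 0.800 / 0.801 | 0.800 / 0.802 | 0.801 / 0.800 |
| 0 | 0.5 | 0.801 | 0.801 / 0.801 | 0.802 / 0.799 | 0.801 / 0.801 |
| 0.5 | 0.3 | 0.800 | 0.840 / 0.837 | 0.815 / 0.823 | 0.800 / 0.799 |
| 0.5 | 0.5 | 0.800 | 0.870 / 0.862 | 0.828 / 0.835 | 0.801 / 0.798 |
| 1.0 | 0.3 | 0.801 | 0.885 / 0.877 | 0.832 / 0.840 | 0.800 / 0.803 |
| 1.0 | 0.5 | 0.803 | 0.948 / 0.930 | 0.856 / 0.870 | 0.801 / 0.803 |

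With a true ratio of 1.00 and g of 0.5 or 1.0, the activity halves ran from 1.047 to 1.182 and the disposition groups from 1.019 to 1.088, while the overall estimate stayed between 0.999 and 1.002.

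**5. Reading the table.** Bias appears only when treatment moves the stratifying variable. It pushes both strata the same way, towards a smaller saving, and leaves the two strata close to each other. The overall estimate and the split on a baseline variable recover the truth to within simulation error.

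**The case against.** **Daily activity level might be a baseline measure.** It is undefined, and the Protocol collects "Activities of daily living: admission to discharge; admission to 30-day post-discharge" at minus "30, admission, discharge, +30". A value from before or at admission would escape the objection. This is a fair limit. But the Protocol gives that scale its own name, and its measures of activity by day are the tracker ones. If the scale was meant, the text still needs to say so.

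**Nothing shows that treatment changes disposition.** This stands. Its timing after treatment is certain, but an effect on it is inferred from its listing as a utilization outcome. Without such an effect the bias vanishes, as the g = 0 rows show.

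**Tracker data in the controls are not documented.** The controls are patients who were not enrolled, assessed retrospectively, and the tracker rows name no inpatient source. This stands, but it is no defence: without control data, a tracker-activity subgroup comparison could not be run at all.

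**The numbers depend on chosen slopes.** They do. The Protocol supplies none.

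A reader might also infer that these subgroups would point to the wrong patients for home hospital. The simulation does not support that: the two strata give nearly equal ratios, so it shows a saving understated in both rather than false heterogeneity. Nor are in-stay activity or discharge disposition known when home hospital is offered. A reader might equally take these to be declared subgroups of the cost outcome. Cost is probably included, but the sentence names no outcome.

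**Conclusion.** The point holds as a caution about two of the five planned subgroup variables. Disposition is certainly recorded after treatment starts; daily activity level most naturally is too. Effects within these strata are likely to be biased where treatment moves the variable and severity drives both it and the outcome. For activity, the first condition rests on the investigators' own earlier result and the second is clinically plausible. For disposition, an effect of treatment is plausible but undocumented. Baseline weighting does not remove the bias.

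Its size cannot be computed from the Protocol. Under the assumed slopes with a non-zero treatment shift, a uniform 20% saving appears as roughly 5% to 16% in the activity halves and 13% to 18% in the disposition groups. These are illustrations, not estimates for this study. The whole-group analysis and the subgroups by diagnosis, age group and location of admission are untouched, so the text should be corrected but the main comparison is not in doubt.

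**What to change.** In the Quantitative section, state that subgroup variables are limited to values known at or before admission. Remove disposition from the list. Replace daily activity level with a named baseline measure already collected: activities of daily living at 30 days before admission or at admission, PRISMA-7, or use of a home health aide before admission. Report disposition and tracker activity as outcomes; if a breakdown by either is still wanted, label it descriptive and not an estimate of the effect of home hospital. Confirm that the same restriction applies to the early-transfer and paramedic analyses that refer back to this section.

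The cost is a change of wording. No new data, visits or sample size are needed.
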